#### 15.3 Statistical Analysis:

Absolute SU changes from baseline to week 8 will be calculated using multiple linear regression adjusting for patients' characteristics including age, gender, BMI, renal function, and concomitant medications. Genetic variants and microbiome features will be tested with forward stepwise regression.

Overall differences in microbiome composition from baseline to week 8 will be compared using three principle axes of variation in the microbiome. A linear regression will be analyzed with a bacterial taxon as dependent and host factors as independent variables. The significance of association of a host factor will be determined by the test of the null hypothesis that the coefficient is equal to zero. For microbiome features, we will correct computed p-values for the total number of comparisons between dependent and independent variables using false discovery rate correction.

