### **3.0 Study Endpoints/Events/Outcomes**

3.1 Primary Endpoint/Event/Outcome: Absolute change in serum urate after the 8 week of vitamin C intervention

3.2 Secondary Endpoint(s)/Event(s)/Outcome(s): Secondary outcomes include the followings:

- Change in gout related symptoms measured by Gout Assessment Questionnaire 2.0^15 and number of joints affected by gout using Swollen Joint Count (44 Joints) post-administration of vitamin C
- Change in BMI
- Taxonomic and functional patterns of gut microbiota associated with SU
- Change in taxonomic and functional patterns of gut microbiota post-administration of vitamin C
- Taxonomic and functional patterns of gut microbiota associated with food types that trigger gout

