Urine collection: Participants will be asked to collect one urine sample during the visit. Urine urate and creatinine will be measured. Urine samples will be stored for additional analyses as needed.

**During the 8 Week of Study:** The bilingual (English and Hmong) researchers will contact each participant by phone (either text or phone call as participants desire) at **weeks 1, 4, and 7** during the study to assess any medication safety and tolerance issues, any

medication changes, and remind participants of the importance of precise timing of dosing leading up to final visit.

**Study Visit (Visit 2):** All the information collected in Visit 1 will be collected again at this visit except for informed consent, privacy statement, DNA and demographics. This visit will last approximately 120 minutes.

Table 1. Clinical data collected in each study visit

| Items                                                                   | Visit 1  | 4 Phone calls* | Visit 2  | Site** |
|-------------------------------------------------------------------------|----------|----------------|----------|--------|
| Informed consent and privacy statement (HIPAA)                          | X        |                |          | A/B    |
| Demographics                                                            | X        |                |          | A/B    |
| Anthropometrics: height, weight, waist circumference                    | X        |                | X        | A/B    |
| Medical history, including pregnancy status and COVID-19 vaccine status | X        |                | X        | A/B    |
| Medication and dietary history                                          | X        |                | X        | A/B    |
| Vital signs (BP, HR)                                                    | X        |                | X        | A/B    |
| Gout symptoms (GAQ2.0 and swollen joint count)                          | X        |                | X        | A/B    |
| Blood, saliva and urine samples collection                              | X        |                | X        | A/B    |
| Stool samples collection x 2 consecutive days                           | X        |                | X        | B      |
| Medication adherence                                                    |          | X              | X        | A/B    |
| Adverse effects from study medication                                   |          | X              | X        | A/B    |

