## 15.0 Statistical Considerations

### 15.1 Data Analysis Plan:

**Genomic Analysis:** We will collaborate with University of Minnesota Genomic Center (UMGC) to extract and purify genomic DNA, genotyping key variants on transporter genes which associated with urate absorption and reuptake, including *ABCG2* and *SLC22A12*.

**Microbiome Analysis:** We will collaborate with UMGC to extract DNA from the stool sample to sequence whole-genome shotgun sequencing of the microbiota. following the UMGC protocol. Whole-genome shotgun sequencing data will be trimmed and processed for quality using SHI7 and strain-level taxa will be annotated by comparison to a public strain database. Microbiome features (alpha diversity, beta diversity, taxon relative abundance, gene functional category) will be analyzed, as described in a previous study.

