#### 15.2 Power Analysis:

For an effect size of 0.5 mg/dL SU reduction from baseline by vitamin C, using a one-sided *t*-test, 80% power, type 1 error of 0.01, and 15% drop-out rate, 120 in adults with HU and/or gout (standard deviation, SD of 1.5 mg/dL) and 60 adults without HU and gout (SD of 1 mg/dL) are required.

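### The only stated test of microbiome change from baseline to week 8 covers three principal axes, so the secondary outcome of taxonomic and functional change has no matching full-profile or feature-level test

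*Protocol*

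**What the plan says.** All of this is in the protocol.

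- Section 3.2 lists as a secondary outcome "Change in taxonomic and functional patterns of gut microbiota post-administration of vitamin C".
- Section 15.3 states the comparison over time: "Overall differences in microbiome composition from baseline to week 8 will be compared using three principle axes of variation in the microbiome". It does not name the ordination method or the distance, and does not say whether the axes are tested jointly or one by one.
- Section 15.3 then gives a taxon model: "A linear regression will be analyzed with a bacterial taxon as dependent and host factors as independent variables". Its null hypothesis is written out: "The significance of association of a host factor will be determined by the test of the null hypothesis that the coefficient is equal to zero". The host factors are not listed.
- Multiplicity in Section 15.3: "we will correct computed p-values for the total number of comparisons between dependent and independent variables using false discovery rate correction".
- Section 15.1 adds: "Microbiome features (alpha diversity, beta diversity, taxon relative abundance, gene functional category) will be analyzed, as described in a previous study". It does not say whether this is at baseline, between groups or over time.
- Table 1 in Section 5.2 schedules "Stool samples collection x 2 consecutive days" at both visits, so each completer provides paired profiles.

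**The concern.** Principal axes are the directions in which samples differ most. In a set of stool samples from many people, those directions are likely to reflect mainly how people differ from one another. A change within people over eight weeks need not lie along them. The null hypothesis actually tested is therefore no shift on three axes, which is narrower than no change in composition.

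The taxon regression does not fill the gap as written, because the coefficient it tests belongs to a host factor. Functional change, which Section 3.2 names alongside taxonomic change, has no stated contrast between visits.

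At stake is the reading of a null result. It could be reported as no microbiome change after vitamin C when only three directions were examined, although the paired samples hold the information for a wider test.

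**Working it through.** **1. Outcome against stated tests**

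| Place | What is tested | Change between visits? |
|---|---|---|
| 15.3, overall comparison | Position on three axes | Yes, on those axes only |
| 15.3, taxon regression | Host-factor coefficient equals zero | Not as written |
| 15.1, list of features | No hypothesis stated | No contrast given |

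No row has as its null that a given taxon, a given gene category or the whole profile is unchanged at week 8.

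**2. What the three-axis test can see**

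Let d be a participant's week 8 minus baseline profile, with mean δ and covariance Σ over n participants, and let V hold the three axes. A joint test uses the scores V′d, with mean m and covariance S:

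T² = n m′S⁻¹m, and F = T²(n−3) / [3(n−1)] on 3 and n−3 degrees of freedom.

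For fixed axes its noncentrality is n(V′δ)′(V′ΣV)⁻¹(V′δ). If V′δ = 0, this is zero for every n, so more participants do not help. If δ is partly aligned with the axes, power is reduced rather than absent.

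**3. Inputs for an illustration**

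The protocol gives no effect size, variance or feature count for the microbiome, so there is no figure of its own to reproduce. Section 15.2 plans serum urate with "80% power, type 1 error of 0.01, and 15% drop-out rate". Borrowing that drop-out rate: 180 × 0.85 = 153 pairs overall, and 60 × 0.85 = 51 pairs per analysis group. Everything else below is assumed.

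**4. Simulation A: full-profile test**

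There are 200 log-scale features, 20 of them shifted in random directions, and the top three axes carry about 67% of variance. Axes come from pooled samples. Paired t-tests on three scores at 0.05/3 are compared with a within-person sign-flip test of the squared mean difference over all features (199 permutations, 300 replicates).

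| Pairs | Within-person SD | Shift | Three axes | Full profile |
|---|---|---|---|---|
| 153 | 0.5 | 0 | 7% | 4% |
| 153 | 0.5 | 0.10 | 11% | 85% |
| 153 | 0.5 | 0.15 | 16% | 100% |
| 51 | 0.7 | 0.10 | 6% | 13% |
| 51 | 0.7 | 0.15 | 8% | 25% |
| 51 | 0.7 | 0.30 | 12% | 99% |

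The 51-pair rows for shifts 0.10 and 0.15 come from a repeat with similar settings. Other repeats at 153 pairs gave 9.5-11% against 80-86% for shift 0.10, and 16-22% against 99.5-100% for shift 0.15, including one with about 80% of variance on the three axes.

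Direction decides the result:
- Aligning only the signs of the 20 shifts with one leading factor raised three-axis power from 11% to 38% (shift 0.10) and from 16% to 69% (shift 0.15), at 153 pairs.
- Placing a shift of the same size along the leading axis reversed the order: 100% on three axes against 86% for the full profile (153 pairs, SD 0.5, shift 0.10), and 97% against 31% (51 pairs, SD 0.7, shift 0.15).

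**5. Simulation B: feature-level test**

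There are 100 features, within-person correlation is 0.7, and variances are 20, 12 and 8 on three axes and 4 falling evenly to 0.5 on the other 97. The three axes carry 40 / (40 + 97 × 2.25) = 40 / 258.25 = 15.5% of variance. The joint test above at 0.05 is compared with paired t-tests on every feature under Benjamini-Hochberg correction (600 replicates). Shifts are in SDs of the within-person change, on one feature.

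| Pairs | Shift | Three axes | Feature tests |
|---|---|---|---|
| 51 | none | 4.5% | 4.7% |
| 51 | 0.5 SD, leading axis | 79% | 45% |
| 51 | 0.5 SD, off axes | 6% | 48% |
| 51 | 1 SD, off axes | 14% | over 99% |
| 153 | 0.5 SD, off axes | 7% | 99% |

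Tripling the pairs leaves the three-axis test near its 5% level for the 0.5 SD off-axis shift, as step 2 predicts. The pattern holds whether the axes carry about 15% or about 67-80% of variance.

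**The case against.** The strongest reply is that Section 15.1 already commits to beta diversity, taxon abundance and gene categories by the method of a cited study, and that model terms and pairing are commonly left to an analysis plan, which is not at hand. Host factors is also an undefined term. This stands in part. A reader might infer that three axes are the only way change will ever be tested and that the taxon model definitely excludes visit. The documents do not support that: they show only that no other contrast between visits is stated. What remains is that Section 15.3 does fix the comparison over time on three axes and does write out an association null for the taxon model. An analysis plan that merely followed it would carry both forward.

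A reader might also infer that any change off the axes is missed. That is strictly true only for a shift orthogonal to them; a partly aligned shift loses power by degrees.

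Testing a few axes is a recognised summary that limits multiplicity. Its null is narrower, not invalid, and it is the stronger test when the shift follows a leading axis. This stands in full and is the reason to keep it.

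Finally, the power figures depend on chosen inputs. By group, at small shifts, the full-profile test is weak too (13% and 25% at shifts 0.10 and 0.15). This also stands.

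**Conclusion.** The point holds as a mismatch between a secondary outcome and its stated tests. The only explicit test of microbiome change covers three axes, and nothing stated tests the full taxonomic or functional profile, or a single feature, between visits.

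With 153 pairs and a shift largely off the axes, power was about 10-20% on three axes against 80-100% for a paired full-profile test. These figures illustrate the mechanism and do not predict this trial. They rest on an assumed variance structure, assumed shift sizes and random shift directions, and the order reverses for a shift along a leading axis. Leading axes are the natural reading of the text, but the ordination is not specified and axes from a beta-diversity distance were not simulated.

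This is a cheap improvement to a secondary analysis. The primary serum urate result is unaffected.

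**What to change.** In Section 15.3, keep the three-axis comparison and add:

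1. A distance-based permutation test (PERMANOVA) of visit on the full taxonomic profile and on the full functional profile, with visit labels permuted only within participant. As stool is collected on two days per visit, the two samples of a visit should be combined or moved together in the permutation.
2. For single taxa and gene categories, a within-person baseline-to-week-8 contrast with visit as the tested term, under the existing false discovery rate correction.
3. A reporting rule: a null three-axis result is worded as no shift on these axes, not as no change in the microbiome.

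The cost is some wording, a little more computing and a slightly larger set of tests to correct. No new samples or assays are needed.

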#### 15.4 Data Integrity:

Data for this study will be entered into a REDCap database, which uses a MySQL database via a secure web interface with data checks used during data entry to ensure data quality. REDCap includes a complete suite of features to support HIPAA compliance, including a full audit trail, user-based privileges, and integration with the institutional LDAP server. The MySQL database and the web server will both be housed on secure servers operated by the University of Minnesota Academic Health Center's Information Systems group (AHC-IS). The servers are in a physically secure location on campus and are backed up regularly, with the backups stored in accordance with the AHC-IS retention schedule. Backup tapes are stored offsite. The AHC-IS servers provide a stable, secure, well-maintained, and high-capacity data storage environment, and both REDCap and MySQL are widely-used, powerful, reliable, well-supported systems. Access to the study's data in REDCap is restricted to the members of the study team by username and password.

## 16.0 Health Information and Privacy Compliance

16.1 Select which of the following is applicable to your research:

- ☐ My research does not require access to individual health information and therefore assert HIPAA does not apply.
- ☒ I am requesting that all research participants sign a HIPCO approved HIPAA Disclosure Authorization to participate in the research (either the standalone form or the combined consent and HIPAA Authorization).
- ☐ I am requesting the IRB to approve a Waiver or an alteration of research participant authorization to participate in the research.

Appropriate Use for Research:

- ☐ An external IRB (e.g. Advarra) is reviewing and we are requesting use of the authorization language embedded in the template consent form in lieu of the U of M stand-alone HIPAA Authorization. Note: External IRB must be serving as the privacy board for this option.

16.2 Identify the source of Private Health Information you will be using for your research (Check all that apply)

- ☐ I will use the Informatics Consulting Services (ICS) available through CTSI (also referred to as the University's Information Exchange (IE) or data shelter) to pull records for me
- ☒ I will collect information directly from research participants.
- ☐ I will use University services to access and retrieve records from the Bone Marrow Transplant (BMPT) database, also known as the HSCT (Hematopoietic Stem Cell Transplant) database.
- ☐ I will pull records directly from EPIC.
- ☐ I will retrieve record directly from axiUm / MiPACS
- ☐ I will receive data from the Center for Medicare/Medicaid Services
- ☐ I will receive a limited data set from another institution
- ☐ Other. Describe:

16.3 Explain how you will ensure that only records of patients who have agreed to have their information used for research will be reviewed.

N/A. We will not be accessing patients' health records.

16.4 Approximate number of records required for review: N/A.

16.5 Please describe how you will communicate with research participants during the course of this research. Check all applicable boxes

- ☐ This research involves record review only. There will be no communication with research participants.
- ☐ Communication with research participants will take place in the course of treatment, through MyChart, or other similar forms of communication used with patients receiving treatment.
- ☒ Communication with research participants will take place outside of treatment settings. For the safety and adherence to the vitamin C treatment, biweekly phone call contacts will be made.

16.6 Explain how the research team has legitimate access to patients/potential participants:

Several community researchers may have legitimate access to medical records by virtue of their occupation or practice site (physicians, pharmacists). This may be a likely mechanism by which subject recruitment may naturally occur through routine clinical interactions.

16.7 Location(s) of storage, sharing and analysis of research data, including any links to research data (check all that apply).

☐ In the data shelter of the [Information Exchange \(IE\)](#)

☐ Store ☐ Analyze ☐ Share

☐ In the Bone Marrow Transplant (BMT) database, also known as the HSCT (Hematopoietic Stem Cell Transplant) Database

☐ Store ☐ Analyze ☐ Share

☒ In REDCap (recap.ahc.umn.edu)

☒ Store ☐ Analyze ☒ Share

☐ In Qualtrics (qualtrics.umn.edu)

☐ Store ☐ Analyze ☐ Share

☐ In OnCore (oncore.umn.edu)

☐ Store ☐ Analyze ☐ Share

☒ In the University's Box Secure Storage (box.umn.edu)

☒ Store ☐ Analyze ☒ Share

☐ In an AHC-IS supported server. Provide folder path, location of server and IT Support Contact:

☐ Store ☐ Analyze ☐ Share

☐ In an AHC-IS supported desktop or laptop.

Provide UMN device numbers of all devices:

☐ Store ☐ Analyze ☐ Share

☐ Other. Describe:

Indicate if data will be collected, downloaded, accessed, shared or stored using a server, desktop, laptop, external drive or mobile device (including a tablet computer such as an iPad or a smartform (iPhone or Android devices) that you have not already identified in the preceding questions

☐ I will use a server not previously listed to collect/download research data

☐ I will use a desktop or laptop not previously listed

☐ I will use an external hard drive or USB drive ("flash" or "thumb" drives) not previously listed

☐ I will use a mobile device such as a tablet or smartphone not previously listed

*16.8* Consultants. Vendors. Third Parties. De-identified data will be made publicly available during analysis and following publication as is the standard in peer-reviewed medical journals.

*16.9* Links to identifiable data: There will be no links to identifiable data; they will be contained in a Box spreadsheet accessible only to minimal staff necessary to create the de-identified spreadsheet.

*16.10* Sharing of Data with Research Team Members. Data will be shared on Box (box.umn.edu).

*16.11* Storage and Disposal of Paper Documents: Paper documents will be stored in a locked cabinet in the PI's secure lab space and will be destroyed using a commercial confidential paper shredding business.

## **17.0 Confidentiality**

*17.1* Data Security: To ensure confidentiality, all people enrolled in the study will be assigned a study identification code. This code will be used on all study related data collection forms except for those on which the use of personal identifiers is mandatory (e.g., informed consent form). Forms that link the name of the participant and the study identification code will be kept in a locked cabinet inside a locked office under the control/supervision of PI and Co-PIs and in an electronic file stored on a password protected, strongly encrypted computer server that meets HIPAA guidelines. Access to study participants' identifiable

information will be limited to those that require this information such as the principal investigators or others who have direct contact with study participants, such as the bilingual/ bicultural research staff. Any personnel with data access will be identified to the University of Minnesota IRB and listed on the HIPAA form.

## **19.0 Provisions to Protect the Privacy Interests of Participants**

### *19.1 Protecting Privacy:*

Potential participants are encouraged to bring up questions and concerns about study participation. Participants are informed that participation is voluntary; they can refuse to answer any questions or complete any study activities if they feel uncomfortable, and that they may discontinue participation in the study at any time.

To protect the privacy of individuals who choose to participate in this study, testing (questionnaires, biometrics, and biospecimen collection) will be completed in a private space, away from other people. Only one researcher will be with the participant at the time of testing for privacy.

All enrollees will receive a unique study ID code. The study identification (ID) code is how all collected data will be recorded. Forms linking codes to personal identification information for all participants will be secured. All the data will be kept safe and under locked access during and after participants have completed the study based on the database protection policy described below. With study participants' permission for future contact, identifiers will only be available to the PI, the co-investigators, and select key personnel, such as a study coordinator. However, for participants who do not wish to be contacted for future studies, their data will be de-identified and identifiers will no longer be available to co-investigators.

*19.2* Access to Participants:

For participant safety and only with their permission, relevant medical records will be requested and reviewed for any adverse events reported by participants. Participants will be asked to sign a release authorization to grant access to these records. No other type of private records will be accessed for the study.

**20.0 Compensation for Research-Related Injury**

*20.1* Compensation for Research-Related Injury: N/A. This study is minimal risk. Vitamin C is available as an over-the-counter nutraceutical supplement. Treatment plan for acute gout flare will be discussed during enrollment of the study. We will not provide medical treatments or cover the medical costs for acute gout treatment.

*20.2* Contract Language: N/A.

